# Self-management in early-stage dementia: a pilot randomised controlled trial of the efficacy and cost-effectiveness of a self-management group intervention (the SMART study)

**DOI:** 10.1186/1745-6215-15-74

**Published:** 2014-03-08

**Keywords:** Alzheimer’s disease, Vascular dementia, Caregiver, Self-efficacy, Well-being, Support

## Abstract

**Background:**

The possibility of living well with a long-term condition has been identified as centrally relevant to the needs of people living with dementia. Growing numbers of people with early-stage dementia are contributing accounts that emphasise the benefits of actively engaging in managing the condition. Self-management interventions share the common objectives of educating about the condition, optimising well-being, enhancing control over the situation and enabling people to take more responsibility for managing the condition. Benefits of such an approach can include improved knowledge, self-efficacy, health status, and better performance of self-management behaviours. However, there is only preliminary evidence that people with early-stage dementia can benefit from such interventions.

**Methods:**

This feasibility study involves the development of a self-management group intervention for people with early-stage Alzheimer’s disease, vascular dementia or mixed Alzheimer’s and vascular dementia. This study is a single-site pilot randomised-controlled trial. Forty-two people with early stage dementia, each with a caregiver (family member/friend), will be randomised to either the self-management group intervention or to treatment as usual.

The self-management group intervention will involve eight weekly sessions, each lasting 90 minutes, held at a memory clinic in North Wales. All participants will be re-assessed three and six months post-randomisation. This study is intended to supply an early evaluation of the self-management intervention so that a full scale trial may be powered from the best available evidence. It will assess the feasibility of the intervention, the study design and the recruitment strategies. It will estimate the parameters and confidence intervals for the research questions of interest. The primary outcome of interest is the self-efficacy score of the person with dementia at three months post-randomisation. Secondary outcomes for the person with dementia are self-efficacy at six months post-randomisation and cognitive ability, mood and well-being at three and six months post-randomisation. Secondary outcomes for caregivers are their distress and stress at three and six months post-randomisation. The cost-effectiveness of the intervention will also be examined.

**Discussion:**

This study will provide preliminary information about the feasibility, efficacy and cost-effectiveness of a self-management group intervention for people in the early stages of dementia.

**Trial registration:**

Current Controlled Trials, ISRCTN02023181.

While there is evidence for the benefits of self-management interventions, the theoretical bases of these interventions are often not explained [11]. The most common conceptualisation of self-management [12] is based on social cognitive theory [13,14]. Bandura proposed that behaviour is influenced by goals, level of self-efficacy, outcome expectations and various sociocultural factors. Most empirical work has focused on the self-efficacy component of this model. Self-efficacy is defined as the person’s belief that s/he can perform a specific action in a particular situation. Self-regulation offers another theoretical basis for self-management. This theory proposes that self-observation, self-evaluation and self-reactions are the processes by which people learn to deal with complex environments and develop problem-solving strategies [15].

In relation to dementia, there is evidence to suggest that people with early-stage dementia are usually able to identify some issues that they would like to manage better [16]. This offers an avenue for a sensitive and tailored approach to encourage individuals with early-stage dementia to draw on their resources and on support from others to make positive changes. Approaches such as support groups [17], psychotherapy groups [18], goal-oriented rehabilitation [19] and early-stage dyadic interventions [20] support self-management skills by helping people to manage the present and future impact of the condition, identify and implement memory management strategies and plan ahead to take control of legal, financial and health issues. Therefore, there are preliminary, but limited, indications that people with early-stage dementia could benefit from a more focused self-management approach.

While self-management approaches have common components across conditions, these approaches are applied with subtly different emphases depending on the nature of the condition in question; for example, in diabetes there is a focus on self-medicating and self-monitoring [21] while the focus is on managing symptoms and promoting behaviour change in chronic obstructive pulmonary disease [22], asthma [23] and rheumatism [24]. In order to conceptualise self-management in early-stage dementia, it will be important to adapt the approach to take account of condition-specific factors. However, there is limited evidence on which to base the development of self-management approaches for people with dementia. One study explored what people with dementia think should be included in self-management interventions. Although few details were provided about the participants who contributed, suggested emphases included managing dementia alongside other conditions, managing unexpected symptoms, and the importance of maintaining meaningful roles [25]. Two further papers have examined views about self-management held by a range of respondents, including both health professionals and people with dementia. Perceived barriers to self-management included the impact of societal views and public impressions and a general lack of information [26]. Concepts of self-management echoed elements of person-centred care and emphasised the ‘self’ element of self-management by focusing on managing life with dementia rather than managing the dementia itself [27]. However, in these two papers the views of people with dementia were not reported separately from the insights gained from other respondents [26,27]. There is a need for further in-depth investigation of the views of people with dementia and caregivers to help formulate a dementia-specific approach to self-management, which can then be evaluated in terms of feasibility, acceptability and clinical efficacy, and ease of use by clinical teams. The SMART study aims to address this need.

In the first phase of the SMART study, following an initial qualitative investigation in which the perspectives of people with dementia and caregivers were examined, and a review of the literature on the theory and practice of self-management in a range of conditions, a manual for an eight-session group self-management intervention for people with early-stage dementia was developed. The intervention approach is based on self-regulation models and social cognitive theory, and the overall aim is to enhance participants’ self-efficacy and problem-solving skills through focusing on meaningful and relevant aspects of living with dementia. The pilot trial outlined in this protocol is intended to provide preliminary evidence about the feasibility and efficacy of the intervention so that a subsequent full-scale randomised controlled trial (RCT) may be powered from the best evidence available in order to address the following objectives.

The primary objective is to evaluate the effectiveness of the self-management intervention in improving self-efficacy in people with dementia compared to treatment as usual (TAU). The secondary objectives are to evaluate the effectiveness of the self-management intervention in (a) improving mood, well-being and cognitive test scores in people with dementia compared to TAU; (b) decreasing caregiver stress and general distress compared to TAU, and (c) estimating the cost-effectiveness of the self-management intervention compared to TAU and establishing whether it results in a reduction in health service utilisation.

## Methods

### Design

This SMART study involves two phases, following the development and feasibility/piloting phases of the Medical Research Council guidelines for complex interventions [28] and the present paper relates to phase II. In phase I of the study we triangulated evidence from a systematic review and qualitative analysis of interviews with people with dementia and caregivers to inform the development of a protocol for a self-management group intervention. In phase II we will evaluate the group intervention in a single-site, single-blind pilot RCT comparing the self-management group with TAU. Outcomes will be assessed at 3 and 6 months post-randomisation by a researcher blinded to group allocation (Figure 1, CONSORT diagram).

**Figure 1 F1:**
[figure not shown]
Consort diagram.

### Setting and participants

The aim is to recruit 42 people with early-stage dementia and their primary caregivers. The study will proceed in three waves with approximately 14 participants in each wave. The sample size will provide adequate statistical power for a pilot evaluation of the self-management group, and decisions about sample size have been informed by the need to balance the number of participants required to provide an appropriate amount of information for a pilot study with the number that it is feasible to recruit within the study timescale. As this is a pilot trial, particular note will be taken of recruitment and retention rates so that a future definitive study may be accurately powered. All participants will need to provide informed consent. In order to be deemed to provide informed consent, participants will have to demonstrate that they can understand the study information, retain and weigh up this information sufficiently to clearly communicate their decision about participation, and clearly understand the consequences of this decision.

Participants will be identified from a memory clinic in a semi-rural area of North Wales. The inclusion criteria for people with dementia are as follows: 1) participants must be diagnosed with Alzheimer’s, vascular or mixed Alzheimer’s and vascular dementia, according to ICD-10 criteria [29] and in the early stages as indicated by a score of 20 or more on the Mini-Mental State Examination [30]. These diagnoses account for 89% of dementia diagnoses [31] and rarer sub-types of dementia have been excluded here because they involve features that would require a specific approach; 2) participants must be able to provide informed consent; 3) participants may be either taking or not taking acetyl-cholinesterase inhibitors or Memantine. Participants receiving acetyl-cholinesterase inhibitors or Memantine must have been stabilised on their current dose for a minimum of one month prior to baseline assessment, with no plan to change dosage or medication during the course of the study. This is to ensure that change is not confounded by medication effects, and 4) participants must have a caregiver who is willing to participate in the study. Caregivers may be spouses, partners, siblings or adult children of people with early-stage dementia who are involved in providing day-to-day support.

The exclusion criteria for people with dementia are as follows: 1) a history of stroke, significant neurological or psychiatric conditions (for example, psychosis) or brain injury. These conditions may affect cognitive, emotional and behavioural functioning and thus act as confounders; 2) current significant anxiety or depressive disorder that would affect cognitive, emotional and behavioural functioning and thus act as confounders, and 3) inability to speak English sufficiently well to allow completion of the assessment measures.

In addition, participants who are currently attending other group-based psychosocial interventions will not be enrolled in the study until these have been completed.

There are no specific exclusion criteria for caregivers; any caregiver willing to take part together with the person with dementia for whom she or he provides care will be eligible for inclusion.

### Outcome measures

#### Primary outcome measure

The primary outcome measure will be the scores recorded by participants with dementia on the General Self-Efficacy Scale (GSES) [32] at 3 months post-randomisation. The GSES aims to measure a person’s broad and stable sense of personal competence to deal effectively with a variety of stressful situations. The current version of the scale contains 10 items and participants can complete the measure in approximately 4 minutes. The GSES has high reliability, stability, construct and factorial validity. It has demonstrated convergent and discriminant validity [33].

#### Secondary outcome measures completed by people with dementia at baseline, and three and six months post randomisation

An important secondary outcome is the GSES score at 6 months post-randomisation, which will allow us to evaluate whether the effects of the self-management group extend into the medium term.

##### Cognitive functioning

The Addenbrooke’s Cognitive Examination - III (ACE-III) [34] is a brief test sensitive to the early stages of dementia. It measures cognitive ability in five domains: attention (four items), memory (five items), fluency (two items), language (eight items) and visuo-spatial ability (five items). It is administered by the researcher and can be completed in approximately 12–20 minutes. The ACE III has demonstrated convergent validity and internal reliability. It has high sensitivity and specificity in detecting cognitive problems [35].

##### Anxiety and depression

The Hospital Anxiety and Depression Scale (HADS) [36,37] is a self-report measure of symptoms of anxiety and depression. All symptoms that can also relate to physical disorder, such as fatigue, have been excluded, which makes the scale particularly suited to older adults who may experience other medical conditions. It contains 14 items each answered on a 4-point Likert scale (0 = not at all, 3 = very often indeed) though some items are reverse-scored. Subtotals are derived for anxiety and depression. The HADS has been previously employed and validated in people with dementia [38].

##### Well-being/risk

The Clinical Outcomes in Routine Evaluation - Outcome Measure (CORE-OM) [39] is a self-report measure of problem severity. It contains 34 items which are scored on a 4-item Likert scale (0 = not at all, 4 = most or all of the time). It covers four domains: wellbeing, social functioning, problems/symptoms, and risk to self and risk to others, as well as providing a global distress score. The CORE-OM has good internal consistency and test-retest reliability. It also has good convergent validity and shows sensitivity to change [39].

##### Health-related quality of life

The EQ-5D-3L [40,41] was designed to measure health-related quality of life. The assessment has five questions covering five domains (mobility, self-care, usual activities, pain/discomfort and anxiety/depression). Each item is answered on a 3-point scale (level 1 = no problems, level 3 = unable to do or extreme problem doing). A visual analogue scale is also incorporated into the measure and respondents indicate how good their health is at the time of rating on a 0-to-100 scale, with the anchor points being worst (0) and best (100) imaginable health state. The EQ-5D-3L has been used in a UK sample of people with dementia, including early-stage dementia [42]. A systematic review of recent studies using the EQ-5D-3L with people with dementia reported good feasibility and reliability of the instrument [43]. In a French sample of people with dementia the measure has demonstrated acceptability and construct validity, although inter-rater agreement is limited [44]. In other populations the EQ-5D-3L has good test-retest reliability [41].

##### Quality of life

The instrument, the ICEpop CAPability Measure for Older People (ICECAP-O) [45] focuses on a broader sense of wellbeing. It covers the attributes of quality of life that were rated as important by a UK sample of older people. It measures five attributes (attachment, role, enjoyment, security and control) on a 4-point scale (4 = I can have/I am able, 1 = I cannot have/I am not able). This scale has demonstrated acceptability in a sample of UK older adults and there is initial evidence of construct validity [46].

##### Service use

The Client Socio-Demographic and Service Receipt Inventory (CSRI) [47] asks participants about their use of health and social services over the last three months. They are asked to report the frequency and intensity of their service use. It takes approximately 20 minutes to complete. The CSRI has adequate concurrent validity [47]. In the current study, if necessary, the caregiver will be asked to help the person with dementia to complete this measure.

#### Secondary outcome measures completed by caregivers at baseline, and three and six months post-randomisation

##### Caregiver distress

The Neuropsychiatric Inventory Questionnaire (NPI-Q) [48] assesses behavioural and psychological symptoms and covers 12 domains. The 12 items are scored for severity (3-point scale) and for the degree of caregiver distress experienced (5-point scale). It is a self-report measure and can be completed in approximately 5 minutes. The NPI-Q has good internal consistency and test-retest reliability. It has demonstrated construct validity [48].

##### Caregiver stress

The Relative Stress Scale (RSS) [49] is a self-report measure of caregivers’ levels of stress relating to caring for their relative. There are 15 items answered on a 5-point Likert scale (0 = not at all, 4 = always/considerably). The scale comprises three subscales: personal distress, life upset from caregiving and negative feelings. The RSS has factorial validity and adequate internal consistency [50].

##### Health-related quality of life

The EQ-5D-3L [40,41] will be used (see above).

##### Quality of life

The ICECAP-O [45] will be used (see above).

##### Service use

The CSRI [47] will be used (see above).

##### Post-intervention interview

Participant dyads randomised to the self-management group will be invited to take part in a 20-minute semi-structured interview to explore their perceptions and views of the group. This interview will be conducted by the researcher and will be audio-recorded.

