### Procedure

Potential participants will be invited to take part via an invitation letter or via personal contact from a member of the clinical team. Posters and leaflets advertising the study will be displayed at the memory clinic and groups that make use of the service facilities, such as the local Alzheimer’s café, will receive information about the study. As this is a pilot study, a range of recruitment methods is envisaged to inform future multi-centre trials. People interested in taking part will be contacted by a researcher who can provide more information about the study and answer any questions. If the person is interested in taking part in the study the researcher will arrange a meeting. If the person consents to take part in the study, the researcher will make final eligibility checks and carry out the baseline assessments. Participants will be allowed to pace these assessment visits according to their needs. For instance, short breaks will be permissible if participants are fatigued and if necessary two visits will be made to complete the assessments at each data point.

Eligible, consenting participants will be randomised to receive either the self-management group intervention or TAU after baseline assessments. Randomisation will be conducted by the North Wales Organisation for Randomised Trials in Health (NWORTH). Randomisation will be undertaken using a computer-based algorithm. Randomisation will be balanced (one: one dynamic allocation) [51] and will be stratified for mini-mental state examination score (20 to 24, 25 to 25+) and gender.

Follow-up assessments will occur at 3 and 6 months post-randomisation and will be undertaken by a researcher blinded to group allocation. There will be no unblinding of the researcher, and participants will be asked not to tell the researcher whether they attended the group. To assist retention in the study, appointments will be prescheduled with participants, and reminders of upcoming meetings will be sent. Participants who attend the self-management group will additionally be invited to take part in a post-intervention interview to feed back their experiences of attending the group.

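### The interview offered only to intervention dyads is assigned to the researcher whom the article also says will stay blinded, and neither its timing nor a separate interviewer is stated

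*Protocol article*

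**What the plan says.** The Design section describes a "single-site, single-blind pilot RCT" and says: "Outcomes will be assessed at 3 and 6 months post-randomisation by a researcher blinded to group allocation". The Procedure section repeats this: "Follow-up assessments will occur at 3 and 6 months post-randomisation and will be undertaken by a researcher blinded to group allocation". It then goes further, with no time limit: "There will be no unblinding of the researcher, and participants will be asked not to tell the researcher whether they attended the group".

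The section on the post-intervention interview reads: "Participant dyads randomised to the self-management group will be invited to take part in a 20-minute semi-structured interview". The purpose is to learn what the dyads thought of the group. On who does it: "This interview will be conducted by the researcher and will be audio-recorded". The Procedure section mentions the interview again at its end. It names no other interviewer and gives no timing beyond the label post-intervention.

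Under Cognitive functioning, the same term appears for the ACE-III, which is measured at baseline, 3 months and 6 months: "It is administered by the researcher and can be completed in approximately 12–20 minutes".

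**The concern.** The interview is restricted to one arm and its subject is the intervention. It therefore cannot be conducted without learning the allocation of the dyad being interviewed. The article gives the task to *the researcher*, the term it also uses for the person who must not be unblinded and for the person who administers an outcome test.

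Participants know whether they attended the group and the facilitators know who came, so assessor blinding is the only masking the trial has. If it is lost before a follow-up visit, it is lost in one arm only. An assessor who knows that a person attended the group could, without intending to, prompt or score a researcher-administered test differently. The pilot is meant to supply effect estimates for planning a full-scale trial, so a bias of this kind would carry forward into that planning.

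**Working it through.** The plan gives no figure to reproduce. The check sets the sections side by side.

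**1. Who is interviewed.** Only dyads allocated to the self-management group (Post-intervention interview). The Procedure section refers to those who attend the group. On either wording, no TAU dyad is interviewed.

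**2. Who interviews.** *The researcher* (Post-intervention interview). No section names a different or unblinded interviewer. The Analysis section gives the thematic analysis of the transcripts to members of the research team, which does not settle who collects the interviews.

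**3. Who must stay blinded.** Follow-up is assigned to "by a researcher blinded to group allocation" (Design), and Procedure has the same phrase. The next sentence of Procedure then bars any unblinding of *the researcher*. Earlier in Procedure the same term is used for the person who checks eligibility and does the baseline assessments.

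**4. Do 1 to 3 fit together?** If the term means one person throughout, they do not: the person who must not learn who attended is asked to interview only attenders. If it means two people, they can fit, but the article does not say so.

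**5. When the interview could fall.** Only the label post-intervention is given.
- Eight sessions at weekly intervals (Intervention) span 8 − 1 = 7 weeks from first to last.
- Three months is about 52/4 = 13 weeks, and six months about 52/2 = 26 weeks.
- The last session precedes the 3-month visit if the group starts less than 13 − 7 = 6 weeks after randomisation, and precedes the 6-month visit if it starts less than 26 − 7 = 19 weeks after.

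The interval from randomisation to the first session is not stated, so a prompt start is an assumption. Under it, an interview soon after the last session would come before the 6-month assessment and possibly before the 3-month one.

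**6. How many dyads.** With 42 people randomised one to one, about 42/2 = 21 dyads are in the intervention arm. At most about 21 would have their allocation revealed by interview; no TAU dyad would be revealed directly.

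**7. Which outcomes are exposed.** The ACE-III is the only outcome that the article says the researcher administers. The GSES is described as completed by the participant. The HADS, CORE-OM, NPI-Q and RSS are described as self-report. The only help mentioned with any measure is from the caregiver, for the CSRI.

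**The case against.** The strongest reply is that the conflict rests on the definite article. The sentences that assign follow-up speak of a blinded researcher, with an indefinite article and a qualifier, and the study has a research team with at least two raters. The interviewer may simply be another member of that team. This stands as a limit on confidence. It does not remove the inconsistency, because the article never separates the two roles, and the sentence barring unblinding uses the same term as the interview sentence.

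The second reply is timing. If every interview followed that dyad's 6-month assessment, the outcome data would stay blinded. That is correct, and the article does not exclude it. Even so, if one person does both jobs, the unqualified sentence on unblinding would be untrue.

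The third reply is that a journal article commonly leaves staffing and scheduling to the full protocol. Silence on either would be no finding. Here, though, the article does state who interviews and does state an absolute rule, and the two conflict.

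A reader might also infer three stronger things that the text does not support:
- *The primary outcome is compromised.* No section says the researcher helps with the GSES. Participants also know their own allocation already, so an unblinded assessor adds less to a measure they complete themselves.
- *The assessor can identify TAU dyads by elimination.* Interviews are by invitation and may be declined. The absence of an interview makes TAU more likely but does not establish it.
- *The trial can no longer be called single-blind.* That requires both that one person does both jobs and that the interview comes first. Neither is stated.

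**Conclusion.** The concern holds as an inconsistency in the text with a conditional consequence. Taken literally, the sections on design, procedure, cognitive functioning and the interview cannot all be carried out as written. Assessor blinding is actually lost only if the interviewer is also the assessor and the interview comes before a follow-up visit. Both are possible on the wording, and neither is established.

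If both occur, up to about 21 dyads, all in the intervention arm, are unblinded to the assessor. The outcome mainly at risk is the ACE-III, which is secondary. The documents offer no basis for a figure for the resulting bias; any shift one might insert would be an assumption. They do not show that bias will occur, or that the GSES is affected.

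This should be fixed. Confidence is moderate: the wording is clear, but whether one person fills both roles is inferred.

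**What to change.** Amend the Post-intervention interview section in one of two ways:
- the interviews are conducted by an existing member of the research team who performs no outcome assessment in the trial; or
- each interview is held only after that dyad's 6-month assessment is complete.

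In the Procedure section, replace the absolute statement with one the trial can keep, for example: *unblinding of the outcome assessor will be avoided, and any instance will be recorded with its date and the dyad concerned.* Use a distinct term, such as outcome assessor, for the blinded role in the Design, Cognitive functioning and Procedure sections.

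The cost is a wording amendment and some scheduling. A separate interviewer keeps the interview close to the intervention but needs someone available to do it. Several team members already share the transcript analysis, which makes this plausible but does not prove it. Delaying the interview needs no second person, but participants with dementia would recall the group less well. Having the assessor record a guess of allocation at each follow-up is a useful option, but it is not needed to resolve the conflict.
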